### Sample size

Sample size was initially estimated using a repeated-measures ANOVA framework as an approximation of the planned longitudinal analysis, implemented in G*Power software (version 3.1.9.6). A small effect size was assumed (f = 0.10), consistent with meta-analytic evidence from self-determination theory–based interventions (g ≈ 0.40) [14] and body image programs (g ≈ 0.40) [19].

With a significance level of α = 0.05 and statistical power (1 − β) of 0.80, and assuming two groups with three repeated measurements, the minimum required sample size was estimated to be 164 participants (82 per group). To account for an anticipated attrition rate of approximately 20%, the target sample size was increased to 196 participants.

Given the longitudinal design of the study and the use of mixed models for repeated measures (MMRM) as the primary analytical approach, simulation-based power analyses were subsequently conducted in R to obtain more realistic estimates under plausible assumptions.

These simulations incorporated baseline adjustment, within-subject correlation, and missing data patterns consistent with behavioral interventions. Effect sizes were specified in the small-to-moderate range (d ≈ 0.20–0.30), and assumptions regarding residual variability and within-subject correlation were informed by prior literature on autonomous motivation (RAI).

Power was evaluated with respect to the primary contrast at six-month follow-up time point.

Simulation results indicated that the planned sample size provides moderate, and in some scenarios approaching adequate, statistical power under realistic assumptions, while reflecting the inherent variability associated with behavioral and psychological outcomes.

These complementary approaches ensured both consistency with conventional sample size estimation methods and alignment with the planned analytical model.

To account for potential deviations from the target sample size, contingency strategies were pre-specified. If the final sample exceeds the planned size, all participants will be retained in the analyses to maximize statistical power and precision. If the achieved sample size falls below the target, additional recruitment efforts will be undertaken following the same procedures. Based on the initial assumptions, a minimum sample size of 70 participants per group would still provide adequate statistical power (1 − β = 0.80) to detect moderate effects (g ≈ 0.40).

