### Statistical analysis

All statistical analyses will be pre-specified prior to database lock and conducted using RStudio (v.2026.01.1 + 403, Posit Software). Analyses will follow the intention-to-treat principle, as the primary analytical approach. In addition, per-protocol analyses will be conducted as sensitivity analyses to examine the robustness of findings and to account for potential variations in intervention fidelity (e.g., adherence to the full set of sessions). Descriptive statistics will first be calculated for all study variables, including measures of central tendency and dispersion. Assumptions of normality will be assessed using appropriate statistical tests and graphical methods.

To evaluate the effect of the intervention on the primary outcome, a mixed model for repeated measures (MMRM) will be used, including all post-randomization assessments of autonomous motivation toward physical activity (BREQ-3), Fixed effects will include treatment group (experimental vs. control), assessment time, the treatment-by-time interaction, and baseline values of the outcome as a covariate.

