An appropriate covariance structure (e.g., unstructured or alternative based on model fit indices) will be specified to account for within-participant correlations across repeated measurements. The primary endpoint will be the between-group difference at six-month follow-up, while effects at post-intervention will be considered secondary analyses. Least-squares mean differences between groups will be estimated from the model, along with corresponding 95% confidence intervals and p-values. This likelihood-based approach uses all available observed data without imputing missing values and provides valid inferences under the missing at random (MAR) assumption. Secondary outcomes, including satisfaction and frustration of basic psychological needs, physical activity levels, positive body image, and risk of eating disorders, will be analyzed using equivalent MMRM approaches. In cases where parametric assumptions are violated, robust mixed-effects models and bootstrapping procedures will be applied to obtain reliable parameter estimates. Exploratory analyses of the six BREQ‑3 subscales will follow the same mixed‑effects modelling approach. In addition, mediation will be tested with a half-longitudinal model [34]: group is the independent variable, the change in autonomous motivation (BREQ-3 RAI) from T0 to T1 is the mediator, and the changes in physical activity (IPAQ-SF), positive body image (BAS-2), and eating disorder risk (EAT-26) from T1 to T2 are the outcomes. The primary specification is a single-level structural equation model (lavaan) with bias-corrected bootstrap confidence intervals for the indirect effect; a multilevel SEM that accounts for the partially nested delivery subgroups is reported as a sensitivity analysis. Full detail is given in the SAP (see Supporting information S3 File). Statistical significance will be set at p < .05. Effect sizes will be calculated to facilitate interpretation of the magnitude of effects. Ninety-five percent confidence intervals will be reported for all relevant estimates.

To enhance transparency and reproducibility, a complete Statistical Analysis Plan (SAP, v2.0), structured following the template by [35], is provided as supplementary material (S3 File).

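### The primary MMRM lists no baseline-by-time term, which can cost precision at T2 and biases the T2 contrast if baseline-related dropout differs by arm

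*Protocol article*

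**What the plan says.** The Statistical analysis section models the post-randomisation assessments (T1 and T2) with an MMRM. Its listed fixed effects are treatment group, assessment time, "the treatment-by-time interaction, and baseline values of the outcome as a covariate". Treatment-by-time is the only interaction named. On the covariance, "An appropriate covariance structure (e.g., unstructured or alternative based on model fit indices) will be specified". On the target of inference, "The primary endpoint will be the between-group difference at six-month follow-up". The section then says that the likelihood-based approach "provides valid inferences under the missing at random (MAR) assumption". Secondary outcomes are to be analysed with equivalent models.

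The Sample size section plans for "an anticipated attrition rate of approximately 20" per cent and a target of 196 participants. Its simulations used effects of d ≈ 0.20 to 0.30. The Study and participant timeline section puts baseline in January 2027, T1 in March 2027 and T2 in September 2027. Full detail is referred to SAP v2.0, which is not at hand.

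**The concern.** A baseline main effect without a baseline-by-time term gives baseline a single regression slope at both follow-up visits. T1 is about two months after baseline and T2 about eight, so a flatter slope at T2 would be no surprise. The fitted common slope is then a compromise, too steep for T2.

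Two things follow. First, the adjustment at T2 removes less variance than it could. Second, the statement about missing at random needs a correct mean model. With complete data, randomisation balances baseline and a wrong slope does no harm on average. Once participants are lost, the arms observed at T2 can differ in mean baseline, and a wrong slope corrects that imbalance by the wrong amount.

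Dropout of that kind is plausible here. Participants are not blinded. One arm attends six face-to-face workshops, while the other waits and is offered the programme only after T2, a feature that the Ethics and dissemination section expects to help retention. The effect sought is small, so a bias of a few hundredths of an SD matters.

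**Working it through.** **Inputs from the protocol.** N = 196, 1:1 allocation (98 per arm), about 20% loss (196 × 0.80 ≈ 157 seen at T2), primary contrast at T2, unstructured covariance allowed, planning effect 0.20 to 0.30 SD.

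**Assumptions, because the protocol gives no values.** All SDs are 1, so slope equals correlation. Correlations are written in the order T0–T1 / T0–T2 / T1–T2. Loss at T2 is 20%, either at random or rising as baseline falls (log-odds 1 per SD).

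**The plan's own figure.** The protocol gives no figure for the precision or bias of the MMRM. The only sample size it derives by formula is the repeated-measures ANOVA, and that reproduces. With f = 0.10, three measurements and assumed ρ = 0.5, λ = N f² m/(1 − ρ) = 164 × 0.01 × 3/0.5 = 9.84 on 2 and 324 df, and power is 0.805. It does not bear on the baseline term.

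**Mechanism.** Let β1 and β2 be the true baseline slopes at T1 and T2, and b the fitted common slope. Let Δx be the difference between arms in mean baseline among those seen at T2, and κ the regression of the T2 residual on the T1 residual. If everyone is seen at T1,

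bias at T2 = Δx × [(β2 − b) − κ(β1 − b)].

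This is zero if the slopes are equal (b = β1 = β2), and zero if Δx = 0, as when dropout depends on baseline alike in both arms.

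*Worked case, 0.7/0.3/0.5, baseline-related dropout in the experimental arm only.* A large-sample fit gave b = 0.621 and Δx = 0.173.
- Residual variance at T1: 1 − 2(0.621)(0.7) + 0.621² = 0.516.
- Residual covariance: 0.5 − 0.621(0.7 + 0.3) + 0.621² = 0.265.
- κ = 0.265/0.516 = 0.513.
- Bias = 0.173 × [−0.321 − 0.513 × 0.079] = −0.063.

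The fit itself gave −0.064. Here participants with low baseline leave the experimental arm, so the effect is understated. If those with high baseline left, the sign would reverse.

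**Simulation at N = 196.** True effect 0.25 SD, 1,500 trials per row, half of the dropouts also missing T1. The Monte Carlo error of a bias is about 0.14/√1500 = 0.004. The variance ratio is common slope over interaction model.

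| Correlations | Dropout | Bias, common slope | Bias, with baseline-by-time | Variance ratio | Power, common / interaction |
|---|---|---|---|---|---|
| 0.6/0.6/0.6 | random | 0.003 | 0.003 | 0.997 | 0.537 / 0.537 |
| 0.6/0.6/0.6 | one arm | 0.000 | 0.000 | 0.998 | 0.510 / 0.511 |
| 0.7/0.5/0.6 | random | 0.000 | 0.000 | 1.012 | 0.437 / 0.444 |
| 0.7/0.5/0.6 | same in both arms | 0.005 | 0.003 | 1.023 | 0.455 / 0.456 |
| 0.7/0.5/0.6 | one arm | −0.021 | 0.006 | 1.006 | 0.378 / 0.457 |
| 0.8/0.5/0.6 | random | −0.002 | −0.002 | 1.098 | 0.429 / 0.460 |
| 0.8/0.5/0.6 | same in both arms | −0.004 | −0.004 | 1.051 | 0.417 / 0.447 |
| 0.8/0.5/0.6 | one arm | −0.042 | 0.003 | 1.071 | 0.323 / 0.458 |
| 0.7/0.3/0.5 | random | 0.002 | 0.001 | 1.109 | 0.365 / 0.393 |
| 0.7/0.3/0.5 | same in both arms | 0.003 | 0.002 | 1.064 | 0.366 / 0.381 |
| 0.7/0.3/0.5 | one arm | −0.060 | 0.001 | 1.067 | 0.227 / 0.396 |

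**Large-sample bias with unequal slopes.** It is −0.025 to −0.064 SD for one-arm dropout. As a stress case, dropout running in opposite directions in the two arms gives −0.056 to −0.126 SD. With baseline-by-time, it is within 0.003 of zero in every scenario.

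**Sensitivity to the assumptions.** A simulation with true effect 0.30 and a dropout log-odds of 0.9 per SD in the experimental arm gave common-slope estimates of 0.273, 0.251 and 0.241 for 0.7/0.5/0.6, 0.8/0.5/0.6 and 0.8/0.4/0.5 (biases of 0.027, 0.049 and 0.059). The interaction model gave 0.295 to 0.301. The variance excess in the last, steepest set was about 15%. A further run, also with true effect 0.30, gave 0.26 to 0.29.

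**The case against.** The strongest reply is that this belongs to the SAP. The article introduces its list as terms that the model is to include, which need not be a closed list, and it defers to an SAP that is not shown. The term may already be there. That stands as a caution. But the article does name one interaction and enters baseline as a main effect, so as printed the model has a common slope.

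Second, everything depends on unequal slopes, and the protocol supplies no correlations. Its one remark on the point, in the Primary outcome section, is that the scale is stable over time in Spanish samples; it gives no interval or figure. With equal slopes there is neither bias nor loss. This also stands, and is why the sizes are shown as a range that starts at zero.

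Third, a reader might infer that the model forces baseline to predict T1 and T2 equally well. It does not. It fixes a common slope, and slope = correlation × SD(visit)/SD(baseline). A falling correlation is compatible with equal slopes if the T2 SD is larger.

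Fourth, the protocol plans reminders and other retention measures, and nothing in it predicts arm-specific dropout. True, but the open-label, wait-list design makes it plausible. Even a bias of 0.06 SD is only about 0.06/0.14 = 0.4 of a standard error.

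**Conclusion.** The point holds in a conditional form. As listed, the primary model gives baseline RAI one slope at T1 and T2. If the slopes differ, the T2 contrast loses some precision: about 0 to 10% in variance, or at most about 5% in standard error and about 3 points of power when dropout is random or alike in both arms. If baseline-related dropout also differs between the arms, the T2 contrast is biased under data that are missing at random, by about 0.01 to 0.06 SD for one-arm dropout, against 0.20 to 0.30 SD planned. All sizes rest on assumed correlations, 20% loss and an assumed dropout strength.

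Two stronger readings are tempting and not supported. One is that any dropout related to baseline biases the contrast. When it acts alike in both arms, the error in the fitted T2 mean is the same in each and cancels. The other is that the protocol's statement about missing at random is false. It is the usual statement and presupposes an adequate mean model; the common slope is a restriction on which it depends, not a demonstrated failure.

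**What to change.** State the fixed effects of the primary MMRM as group, time, group-by-time, baseline and baseline-by-time, and use the same form in the equivalent secondary models. If SAP v2.0 already contains the term, only the article needs aligning.

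The cost is one degree of freedom per model and one phrase of text. When the slopes are in fact equal, the extra term costs essentially nothing (variance ratio 0.98 to 1.00). The protocol says that recruitment has not begun, so the change can be made before any data exist.

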### Ethics and dissemination

All collected data will be coded through the assignment of a unique identification code to each participant, thereby preventing the inclusion of personally identifiable information in the analytical datasets. The correspondence between identification codes and personal data will be stored in a separate, password-protected file on a secure server. Data management procedures will comply with the European Union General Data Protection Regulation [33]. Given the low-risk nature of the psychoeducational intervention, no independent Data Monitoring Committee has been established. Study oversight will be conducted by the research team in accordance with ethical approval and institutional guidelines. No formal auditing procedures are planned for this trial, as it involves minimal risk and is conducted within a single institutional setting.

Questionnaires will be administered in digital format through a secure platform with restricted access limited to authorized members of the research team. Upon completion of the study, coded data will be archived in an institutional repository to ensure long-term preservation and availability for verification and secondary analyses, in accordance with the FAIR principles (Findable, Accessible, Interoperable, and Reusable).

The study was approved by the Research Ethics Committee of Universidad Francisco de Vitoria (reference number: 29/2026) and is registered at ClinicalTrials.gov under the identifier NCT07506343. All participants will receive detailed written information regarding the study objectives, procedures, potential risks, and anticipated benefits, and will provide written informed consent before participation. Participants will retain the right to withdraw from the study at any time without academic or personal consequences. Any important modifications to the study protocol (e.g., changes to eligibility criteria, outcomes, or analysis plan) will be submitted for approval to the Research Ethics Committee of Universidad Francisco de Vitoria prior to implementation. Approved amendments will be updated in the trial registry (ClinicalTrials.gov) and communicated to all members of the research team. When relevant, participants will be informed of any changes that may affect their participation, and they will be provided with information regarding the study results, communicated using terminology that is appropriate and comprehensible.

No physical risks are anticipated as a result of participation in the intervention. However, given the inclusion of sensitive questionnaires related to body image and eating disorder risk, a participant well-being protocol will be implemented. This protocol includes referral to university psychological support services if risk indicators are identified. No financial compensation will be provided; however, equity will be ensured by offering participants in the control group full access to the intervention program after completion of the follow-up assessment.

The wait-list control design was selected for both methodological and ethical reasons. From an ethical perspective, it ensures that all participants will eventually have access to the intervention, which is particularly relevant in university-based preventive programs targeting body image and motivational processes. Methodologically, this design may enhance participant retention and reduce attrition bias. Moreover, the use of a wait-list rather than an active or minimal-intervention control condition allows clearer detection of intervention-specific effects on perceived autonomy support and motivational regulation.

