### Randomization, blinding, and allocation

Following baseline assessment, participants will be randomly allocated to either the experimental or the control group in a 1:1 ratio. The allocation sequence will be generated in R using the *blockrand* package by an independent researcher not involved in participant recruitment, intervention delivery or outcome assessment, with a random seed kept confidential until recruitment is complete.

Block randomization will be used, with permuted blocks of variable size (4, 8, and 12) and 1:1 allocation within each block, without stratification given the homogeneity of the target population in age and academic context. Using variable block sizes that are not disclosed to enrolling staff preserves allocation concealment by preventing prediction of forthcoming assignments, while ensuring balanced group sizes throughout recruitment and minimizing selection bias.

Recruiting and enrolling staff remain masked to the allocation sequence and to the (variable) block sizes throughout the trial. As a post-hoc verification of the absence of allocation selection bias, a Berger–Exner test will be applied to check for any association between the allocation sequence and baseline prognostic characteristics.

Due to the nature of the psychoeducational intervention, blinding of participants and intervention providers (facilitators) will not be feasible. Outcome data will be collected using self-administered standardized questionnaires, minimizing assessor-related bias.

Researchers involved in data management and statistical analysis will remain blinded to group allocation until the primary analyses are completed. Data will be coded using anonymized group identifiers to ensure concealment during analysis.

This approach ensures appropriate separation between sequence generation, allocation concealment, and blinding procedures, in accordance with established guidelines for randomized controlled trials.

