#### Experimental intervention.

Participants assigned to the experimental group will take part in a face-to-face psychoeducational program consisting of six 60-minute group workshops, conducted in small groups of up to 15 participants. Each participant remains in the same delivery subgroup across the six sessions. This format facilitates social interaction and the creation of a need-supportive climate, factors identified as relevant in interventions based on Self-Determination Theory (SDT). Sessions are facilitated by trained professionals with experience in exercise science and psychonutrition, who receive standardized training prior to intervention delivery to ensure consistency across groups. Facilitators complete standardized training covering SDT principles, functionality‑based body image strategies, session structure, and fidelity procedures. The intervention includes structured presentation slides, participant worksheets, guided experiential activities, and reflective exercises. Detailed intervention materials are available from the authors upon reasonable request. Minor contextual adaptations (e.g., examples or wording adjustments) may be made, but core intervention components remain unchanged. The intervention will be delivered following a standardized manual based on established SDT techniques, including autonomy support, structure, and involvement [13,14], as summarized in Table 1.

**Table 1 pone.0355374.t001:** Structure, objectives, and Basic Psychological Needs-Supportive Strategies targeted in the intervention workshops.

Workshop	Primary focus	Need-Supportive Strategies (SDT-based)	Basic Psychological Needs targeted
1	Awareness of motivational quality toward PA	Providing a meaningful rationale: explaining the “why” behind PA engagement.	Autonomy
2	Personal values and autonomously chosen goals	Autonomy support: promoting the internalization of PA goals based on personal interests.	Autonomy & Competence
3	Perceived competence and flexible planning	Structure: providing clear guidance, mastery-oriented feedback, and skill-building for PA.	Autonomy & Competence
4	Positive body image from a functionality-oriented perspective	Acknowledging perspectives: validating participants’ feelings and fostering intrinsic values.	Autonomy & Relatedness
5	Social support and supportive relational climate	Involvement: fostering a warm, supportive, and non-judgmental climate for PA.	Relatedness

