6	Maintenance of change and management of difficulties	Action planning: identifying future supports and strategies for managing PA challenges.	Competence

**Note:** SDT = Self-Determination Theory; PA = Physical Activity.

Each workshop combines brief psychoeducational content with interactive, experiential activities designed to promote reflection, personal meaning, and supportive peer interaction. Activities are structured to support autonomy (choice provision, validation of personal perspectives), competence (mastery‑oriented tasks, individualized progress‑focused feedback), and relatedness (collaborative group climate). This multicomponent structure aligns with evidence identifying these elements as key mechanisms for enhancing autonomous motivation in health‑behavior interventions [14,15].

A distinctive feature of the program is the incorporation of functionality‑oriented body image content. This approach shifts attention from appearance to bodily capabilities and has been associated with improvements in body appreciation and reductions in ED‑related risk factors among young women [16–18]. Integrating functionality appreciation within an SDT‑based framework is expected to reduce appearance‑based exercise motives and reinforce autonomous regulation, helping prevent maladaptive patterns such as compulsive or guilt‑driven exercise [8,9].

Across the six workshops (Table 1), participants will progressively work on: (1) awareness of motivational quality toward exercise; (2) identification of personal values and self‑endorsed goals; (3) competence development through flexible planning; (4) functionality‑focused body appreciation; (5) strengthening social support; and (6) maintenance of behavior change and management of challenges. Fidelity will be monitored using session checklists completed after each workshop. This design integrates components targeting motivational and psychosocial processes identified as relevant factors in the prevention and reduction of eating disorder symptomatology and other health-related behaviors [19,24]. Participants in both groups will be asked to maintain their usual lifestyle habits throughout the study period, and no restrictions will be imposed on concurrent physical activity or health-related behaviors.

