### Wait-list control condition

Participants assigned to the control group will remain on the wait-list during the intervention and follow-up periods and will not receive any specific intervention. To ensure intervention equity, they will be offered access to the full program upon completion of the T2 assessment.

Participants in both groups will be allowed to continue their usual activities and access external health-related services (e.g., psychological support, personal training, or dietary counseling) throughout the study period. To monitor potential sources of contamination, participants will be asked to report any engagement in such services during the study.

These data will be recorded and considered in the interpretation of the findings. If deemed necessary, additional sensitivity analyses will be conducted to explore the potential impact of external interventions on the study outcomes.

All protocol deviations, including non-adherence to the intervention or engagement in external programs, will be documented and reported following established guidelines for randomized controlled trials.

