**Fig 1 pone.0355374.g001:**
[figure not shown]
Participant timeline: Schedule of enrollment, interventions, and assessments. ^a^ Timepoints correspond to baseline (T0), immediate post‑intervention (T1), and six‑month follow‑up (T2). No additional time windows are required because all assessments are scheduled within fixed, predefined periods. ^b^ The intervention is delivered across six structured weekly group workshops; therefore, the arrow does not indicate uninterrupted delivery but rather a multi‑session structured psychoeducational program. ^c^ The control group does not receive any active intervention during the trial period and will be offered access to the full program only after completing the follow‑up assessments at T2.

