Nevertheless, certain limitations should be acknowledged. Conducting the trial within a single university may restrict generalizability to other cultural or institutional contexts, particularly given known differences in PA norms and body image constructs across cultures [28,30]. Blinding of participants and facilitators is not feasible, common in educational and psychosocial interventions, which may introduce social desirability bias [6,15]. The use of self-report measures poses additional challenges: IPAQ-SF may overestimate vigorous PA [29], while the EAT‑26 identifies risk but does not provide diagnostic classification [32]. Finally, although the six-month follow-up assesses medium-term maintenance, longer-term evaluations would be necessary to examine deeper internalization processes and the stability of motivational regulation over time [16]. Because all eligible students are invited (census invitation), self-selection operates at the response rather than the invitation stage: who respond may already be more motivated, which threatens external validity (generalisability) more than the internal validity of the randomised comparison. Rather than merely acknowledging this, the response rate is reported, respondents are compared with the full eligible population, and a post-stratification / inverse-probability-of-response weighting sensitivity analysis probes the robustness of estimates to volunteer bias [37,38]. Residual selection on unobserved characteristics (e.g., baseline motivation) cannot be fully excluded.

Beyond these limitations, this protocol also contributes to ongoing theoretical discussions within SDT research. While the present study focuses on the roles of need satisfaction and need frustration, emerging conceptual work has proposed the additional construct of “need unfulfillment,” describing situations in which psychological needs are neglected rather than actively thwarted [39]. Future research could extend the present design to examine how these distinct need states influence motivational processes in physical activity contexts.

Despite these limitations, the present trial has the potential to make meaningful contributions. If effective, it may offer a scalable, theory-driven model for promoting sustainable PA engagement and positive body image in young women, a group affected by appearance pressures and ED risk [5,7].

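### The protocol credits the wait-list with clearer detection of intervention-specific effects, but this comparison gives only the effect of the whole programme, attention and expectancy included

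*Protocol article*

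**What the plan says.** Ethics and dissemination gives an ethical and a methodological rationale for the comparator. Part of the methodological rationale is that choosing a wait-list in place of an active or minimal control "allows clearer detection of intervention-specific effects on perceived autonomy support and motivational regulation".

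The rest of the article describes the comparison as follows.

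- **Experimental arm** (Experimental intervention): "six 60-minute group workshops, conducted in small groups of up to 15 participants", led by trained facilitators.
- **Control arm** (Wait-list control condition): participants "will remain on the wait-list during the intervention and follow-up periods and will not receive any specific intervention". The footnote to Fig 1 agrees: "The control group does not receive any active intervention during the trial period".
- **Blinding** (Randomization, blinding, and allocation): "blinding of participants and intervention providers (facilitators) will not be feasible". Outcomes come from self-administered questionnaires.
- **Primary endpoint** (Statistical analysis): the between-group difference in the Relative Autonomy Index (RAI) at six months, with two arms.
- **Limitations** (Discussion): "Blinding of participants and facilitators is not feasible, common in educational and psychosocial interventions, which may introduce social desirability bias". Attention, expectancy and the choice of comparator are not mentioned.

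**The concern.** The sentence ranks types of control by how well they show specific effects, and the ranking is the wrong way round. A control that shares general attention and expectancy with the programme is the one that removes them from the contrast. A wait-list leaves them in.

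What is at stake is interpretation. The Discussion presents autonomous motivation as a mechanism that links need-supportive components to physical activity, and describes the programme as built on identifiable active ingredients. H6 takes group as the independent variable and the change in RAI from T0 to T1 as the mediator. The rationale in Ethics and dissemination is the only place where the article argues that its comparator supports a specific attribution. If that sentence stands, a positive RAI result can be reported as evidence for the SDT and functionality content in particular, which these two arms cannot show.

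**Working it through.** No figure in the protocol decides this point, so there is no stated number to reproduce. The check sets the descriptions side by side and asks what the primary contrast contains.

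**1. How the arms differ.** The experimental arm receives 6 × 60 min = 360 min = 6 hours of facilitated group work, and the control arm receives none before T2. Participants in both arms know their allocation. Both arms complete the same assessments at T0, T1 and T2.

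**2. What the contrast estimates.** Write, additively for simplicity:

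- S = effect of the programme's specific content, including the group climate that is designed to support relatedness;
- A = effect of general attention and of expecting benefit, or of knowing that one is waiting.

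Then:

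- experimental minus wait-list = S + A;
- experimental minus a control matched on attention and expectancy = S.

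The trial observes only the first difference. That is one equation in two unknowns, so S is not identified at any sample size. An analysis plan for these two arms could separate S from A only by adding assumptions that the data cannot check. Any reporting bias from unblinded self-report adds a further term, and the limitations already acknowledge that one.

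**3. What a significant result would show.** This is an illustration only, on an assumption that the documents do not supply. Suppose S = 0 and A alone gives a standardized difference d of 0.20 to 0.40. For a two-sample t-test at two-sided 0.05 without baseline adjustment, the noncentrality is d × √(n/2).

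| n per group | d = 0.20: noncentrality | d = 0.20: P(significant) | d = 0.40: noncentrality | d = 0.40: P(significant) |
|---|---|---|---|---|
| 82 | 0.20 × √41 = 1.28 | 0.25 | 0.40 × √41 = 2.56 | 0.72 |
| 98 | 0.20 × √49 = 1.40 | 0.29 | 0.40 × √49 = 2.80 | 0.80 |

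Here 82 per group is the protocol's minimum and 98 is half of its target of 196. A significant primary result is therefore compatible with no specific effect. The conclusion rests on step 2, not on this table.

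**4. The mediation path.** In the H6 model the path from group to T0–T1 change in RAI is also an experimental-versus-wait-list contrast. It carries S + A on the mediator in the same way.

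**5. The named construct.** The battery is BPNSFS, BREQ-3, IPAQ-SF, BAS-2 and EAT-26. The protocol describes the BPNSFS as measuring satisfaction and frustration of autonomy, competence and relatedness, and the BREQ-3 as measuring regulation types. None is described as measuring perceived autonomy support.

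**The case against.** The strongest reply is that clearer detection may only mean a larger contrast. An active or minimal control with facilitator contact could itself deliver some rationale, autonomy support or relatedness and so dilute the difference. It is true that a wait-list can enlarge the total contrast. But the sentence speaks of intervention-specific effects and sets the wait-list against active and minimal controls. A larger total is not a clearer view of the specific part.

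Three further objections stand, and they limit the point.

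- **Group contact is partly intended content.** The small-group format is meant to create a need-supportive climate, Workshop 5 is devoted to it, and a collaborative group climate is listed as the means of supporting relatedness. The 6 hours are largely the dose of the programme and do not measure confounding. General attention and expectancy remain mixed in.
- **The control is no intervention rather than no contact.** Controls consent, complete three assessments, report any use of outside services and are promised the programme after T2.
- **The stated aim and primary endpoint concern the programme as a whole.** No planned analysis described in the article assigns the RAI effect to separate components. The fault lies in the justification and the inference it invites.

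A reader might infer that the wait-list is an unsound comparator, that the primary test is invalid, or that another arm is needed. The documents do not support this. A wait-list is a legitimate comparator for programme versus no programme, which is the question the primary analysis asks. Nor do the documents support any particular split of the planning effect into specific and non-specific parts.

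**Conclusion.** The sentence claims a property that the design lacks, and it names a construct that no listed instrument is described as measuring. The primary contrast estimates the effect of being offered the whole programme against no intervention, with general attention and expectancy included. The limitations disclose social desirability bias only, so the reader is not told of this limit.

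Severity is low. The primary test, the wait-list and its ethical rationale are unaffected; only the conclusion that may be drawn narrows. The size of the non-specific part cannot be stated from the documents. The verdict rests on the protocol's own description of the two arms, the lack of participant blinding and the self-reported outcomes. It needs no assumption about how large attention or expectancy effects are, only that they may not be zero.

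**What to change.** 1. In Ethics and dissemination, replace the sentence with a statement that the trial estimates the effect of being offered the whole programme compared with no intervention, including general attention and expectancy. Say that effects, including the group-to-RAI path in the H6 mediation, will not be attributed specifically to the SDT or functionality components. Use no intervention rather than no contact.
2. Delete perceived autonomy support from the sentence.
3. In the limitations paragraph of the Discussion, add that the comparator does not separate specific content from attention and expectancy, next to the existing remark on blinding.

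The wait-list and its ethical rationale can stay. The change touches no arm, outcome, sample size or analysis, and recruitment had not begun when the article was submitted. The cost is a slightly less favourable stated conclusion.
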